## Abstract

**Background:**

Observational studies have documented a potential protective effect of physical exercise in older adults who are at risk for developing Alzheimer's disease. The Fitness for the Ageing Brain II (FABS II) study is a multicentre randomized controlled clinical trial (RCT) aiming to determine whether physical activity reduces the rate of cognitive decline among individuals with Alzheimer's disease. This paper describes the background, objectives of the study, and an overview of the protocol including design, organization and data collection methods.

**Methods/Design:**

The study will recruit 230 community-dwelling participants diagnosed with Alzheimer's disease. Participants will be randomly allocated to two treatment groups: usual care group or 24-week home-based program consisting of 150 minutes per week of tailored moderate physical activity. The primary outcome measure of the study is cognitive decline as measured by the change from baseline in the total score on the Alzheimer's disease Assessment Scale-Cognitive section. Secondary outcomes of interest include behavioral and psychological symptoms, quality of life, functional level, carer burden and physical function (strength, balance, endurance, physical activity). Primary endpoints will be measured at six and twelve months following the baseline assessment.

**Discussion:**

This RCT will contribute evidence regarding the potential benefits of a systematic program of physical activity as an affordable and safe intervention for people with Alzheimer's disease. Further, if successful, physical activity in combination with usual care has the potential to alleviate the symptoms of Alzheimer's disease and improve its management and the quality of life of patients and their carers.

**Trial Registration:**

Australia New Zealand Clinical Trials Registry ACTRN12609000755235

## Background

Advancing age increases the risk of dementia [1], of which Alzheimer's disease (AD) is the most common cause. Available projections indicate that the number of people with dementia worldwide will increase from 35.6 million in 2010 to 115.4 million people by 2050 [2], with dementia expected to become the major social and economic health challenge of the 21^st ^century.

Alzheimer's disease is characterized by a progressive deterioration in memory and other higher cortical functions that ultimately leads to a loss of independent living skills [3]. Despite the availability of palliative medication with cholinesterase inhibitors and memantine [4], there is currently no cure for AD. There is growing evidence that some environmental factors such as physical and cognitive activity [5,6], decrease the risk of AD [7] and improve the behaviour of patients [8], but it is unclear if such lifestyle interventions can also delay the progression of cognitive decline once the diagnosis of AD has been established [9].

Prospective cohort studies indicate that PA is associated with reduced incidence of dementia [10]. Middleton et al. [11] reported that women who were physically active across the life course had a lower prevalence of cognitive impairment in later life. The association between PA and cognitive function was evident even when exercise is limited to later life [12]. However, as Leone et al. [13] noted, these findings are limited by methodological issues such as survivorship bias and confounding, the latter arising because the exposure to PA is not random in observational studies.

A recent randomised trial (RCT) showed that six months of PA decreased the rate of cognitive decline in older people with subjective memory complaints or Mild Cognitive Impairment (MCI) [14], a group that is at increased risk of developing AD [15]. Subsequently, Baker and colleagues [16] found that six months of high-intensity aerobic activity (75-85% of heart rate reserve) improved executive control processes in sedentary women with MCI. Possible mechanisms mediating the cognitive enhancing effect of PA include alterations of cerebral vascular functioning and brain perfusion, environment enrichment and stimulation of synaptogenesis [14]. A Cochrane review of PA trials for individuals with MCI is currently under way [17].

Few RCTs of PA in AD have been published to date. Most evidence in this area comes from studies conducted with nursing home residents or participants with moderate to severe AD, and the primary outcomes of interest tend to be functional status and/or mood [8,18-20]. The intervention provided in the largest trial, with 134 participants from five nursing homes, was a group-based multi-component exercise program [18]. After 12 months, participants in the exercise group experienced a slower decline in their performance of activities of daily living than those in the control group, but there was no change in behavioural or psychological symptoms (BPSD). In a pilot RCT, Steinberg et al. [19] examined the effect of a home-based, carer-supervised program of walking, strength training and balance exercises on cognition, secondary to measures of functional performance, in 27 people with AD. Although the small sample size likely precluded finding any significant differences between groups in cognitive functioning, the investigators found that the exercise program was safe, could be supervised by caregivers and had good compliance.

The objectives of the present study are to conduct a methodologically rigorous RCT investigating the potential benefits of PA on cognition, well-being, function and BPSD in community-dwelling participants diagnosed with mild to moderate AD. We will also examine whether the intervention eases stress and burden of care, an area that is often neglected in such RCTs [21]. This paper describes the design of the Fitness for the Ageing Brain Study II (FABS II).

## Methods/Design

### Study Design

FABS II is a single blind RCT (Figure 1). The CONSORT statement has been used as a framework for development of the methodology for this project.

**Figure 1 F1:**
[figure not shown]
**Study Design**.

### Participants

230 community-dwelling older adults diagnosed with AD will be recruited across three sites in Australia (Melbourne, Perth and Brisbane). Participants will be included in the study if they satisfy the following criteria: (i) diagnosed with probable or possible AD according to NINCDS-ADRDA criteria [3], (ii) score of 10 or greater on the Standardised Mini Mental State Examination (SMMSE) [22], (iii) community dwelling, (iv) no clinically significant depression, (v) understands written and spoken English, (vi) contact with a friend or family member (carer) for at least 10 hours per week, who is also willing to participate in the trial, and (vii) no other major neurological history or medical condition that contraindicates PA.

Participants will be excluded if they have limited mobility (e.g. unable to walk alone or require a walking aid for balance), show evidence of clinically significant aphasia or pervasive depression, current history of alcohol dependence, have an unstable or life-threatening medical condition, or are participating in another RCT.

Diagnosis of AD will be confirmed through medical records obtained from the participant's treating general practitioner and specialist. These records will be reviewed by members of the research team who are either experienced Geriatricians or Old Age Psychiatrists to confirm the participant's suitability for inclusion.

This study is funded by the National Health and Medical Research Council of Australia. Ethics approval has been obtained from the Human Research Ethics Committee(s) of each participating site and the project complies with the Declaration of Helsinki.

### Recruitment and Screening

Potential participants and their carers will be identified and recruited via local physicians, Memory Clinics and specialists. Additionally, flyers advertising the study and media activities will invite suitable older adults living in the community to consider participation. The research team will contact the participant and next of kin by telephone to check the suitability of the participant according to the study inclusion and exclusion criteria using a strict screening protocol. The 15-item Geriatric Depression Scale (GDS - 15) [23] is included as part of the phone screening to establish the presence of clinically relevant symptoms of depression, excluding potential participants with a score of 6 and higher. The name and contact details for the participant's GP and specialist will be obtained, and the participant will be asked to sign and return a release of medical information form to allow the study team to access their medical records. The participant's GP will also be asked to consent to their patient's involvement in the study. This is another way of determining the suitability of FABS II for the potential participant and ensuring his/her safety during the course of the trial.

### Assessments

Participants will be assessed at baseline and after six months and twelve months in the study (see Table 1 for an overview). There will be two components to the assessments comprising cognitive measures and physical function measures/physical activity questionnaires. Unless stated otherwise, all measures will be administered at each time point. The research assistant (RA) administering the cognitive assessment (Cognitive RA) will be trained by either a Geriatrician or an Old Age Psychiatrist at each site. To ensure that the Cognitive RA remains blind to study group allocation, the physical assessments will be conducted by a separate PA RA. The PA RA will collect demographic and health information via participant interview. The PA RA at each site will be trained by the same chief investigator with a background in exercise physiology to ensure standardization of procedures across all three sites.

**Table 1 T1:** Outline of the assessments and timelines of the FABS II.

*Assessment Tool*	Telephone Screen	Baseline (0 weeks)	Post-Intervention (24 weeks)	12 months (52 weeks)
Geriatric Depression Scale - 15 item	X	X	X	X

Cambridge Contextual Reading Test		X		

Alzheimer's disease Assessment Scale - Cognitive section		X	X	X

Standardized Mini-Mental State Examination		X	X	X

Clinical Dementia Rating Scale		X	X	X

Quality of Life - AD		X	X	X

Neuropsychiatric Inventory		X	X	X

Instrumental Activities of Daily Living		X	X	X

Activities of Daily Living		X	X	X

Short Form-36 version 2 (SF-36v2)		X	X	X

Zarit Burden Interview		X	X	X

Resting blood pressure		X	X	X

Height, weight, body composition, girths		X	X	X

Step test		X	X	X

Sit-to-stand test		X	X	X

Grip strength		X	X	X

Timed Up and Go test		X	X	X

Two-minute walk		X	X	X

Community Healthy Activities Model Program for Seniors (CHAMPS) questionnaire		X	X	X

Stages of Change		X	X	X

Satisfaction with Life		X	X	X

Self-Efficacy Questionnaire		X	X	X

DNA sample collection		X		

The × indicates at which point of the trial the respective assessments took place. Follow-up times relate to baseline testing.

#### Measures administered by the Cognitive RA

The total score on the Alzheimer's disease Assessment Scale - Cognitive section (ADAS-cog) [24] will be the primary outcome measure of the study. The ADAS-cog consists of an 11-item battery of short neuropsychological tests and is widely used to monitor the progression of cognitive deficits in clinical trials with patients with AD. Here we will use a version incorporating a delayed verbal recall task. Higher scores indicate increased severity of cognitive impairment (maximum score is 85).

The following nine assessments comprise the secondary outcome measures. The Cambridge Contextual Reading Test (CCRT) [25] includes the words of the National Adult Reading Test (NART), embedding them within appropriate semantic and syntactic contexts to provide a reliable measure of pre-morbid intelligence. The CCRT is only administered at baseline.

The SMMSE [22] is a modified version of the traditional MMSE [26], which benefits from greater objectivity through more specific scoring examples as well as alternatives for repeated testing of the registration and delayed recall items. A score of less than 10 on the SMMSE will be used to exclude participants, as these individuals would most likely be too cognitively impaired to follow the intervention instructions.

The Clinical Dementia Rating Scale (CDR) [27] is a global rating scale for dementia incorporating information from the primary carer across the domains of memory, orientation, judgment and problem-solving, community affairs, home and hobbies, and personal care. The subscores on each domain are ranked according to severity and an algorithm is used to compute the total score.

The Quality of Life in AD (QoL-AD) [28] is a 13-item questionnaire which requires the participant and carer to independently rate the participant's quality of life across a number of domains on a scale ranging from poor (1 point) to excellent (4 points).

The Neuropsychiatric Inventory (NPI) [29] is a well-established assessment of 12 different BPSD common in AD including delusions, hallucinations, agitation, depression, anxiety, euphoria, apathy, disinhibition, irritability, aberrant motor behaviour, night-time behaviour, appetite and eating disorders. The carer rates each symptom according to the frequency and severity as well as the degree of distress the symptom causes them.

The Instrumental Activities of Daily Living scale (IADL) [30] is widely used to assess independent living skills and is useful in identifying improvement or deterioration over time. The carer rates the AD participant across eight functional abilities, including use of the telephone, shopping, food preparation, housekeeping, laundry, mode of transport, taking medications and handling finances.

The Index of Independence in Activities of Daily Living scale (ADL) [31] is a six-item questionnaire where the carer is required to rate personal and domestic ADLs such as bathing, dressing, toileting, transfers, continence, and feeding. The number of activities in which the participant is deemed 'dependent' is counted.

The Short Form-36v2 [32] is a 36-item questionnaire that assesses the health and well-being of the carer across eight dimensions; physical functioning, social functioning, role limitations due to physical problems, role limitations due to emotional problems, mental health, energy/vitality, pain, and general health perception. Health change over the past year is also assessed. For each dimension of the SF36v2, item scores are coded, summed and transformed on a scale from 0 (worst possible health state measured by questionnaire) to 100 (best possible health state).

The Zarit Burden Interview (ZBI) [33] is a 22-item self-rating scale that examines the degree of burden experienced by the carer associated with functional and behavioural impairments of the person with AD. The items are phrased subjectively and focus on the affective response of the carer.

#### Measures administered by the PA RA

Resting blood pressure will be assessed after a five-minute resting period, with five measurements taken at two-minute intervals with a digital blood pressure monitor (model UA-767PC, A&D Co., Ltd., Saitama, Japan).

Height, body weight, body composition and girths will be measured in light clothing and bare feet. Height will be measured using a fixed stadiometer. Body weight and composition (fat mass, fat free mass) will be assessed using a bio-impedance analyzer, following the procedures provided by the manufacturer (model TBF-300, Tanita Corporation of America, Inc., Illinois, USA). Waist and hip girths will be measured three times (median score used) using a retractable steel tape measure (Lufkin W606PM Cooper industries SC, USA) [34].

A step test using a 7.5 cm square wooden block will be used to assess dynamic balance [35]. The participant places one foot on and off the block as many times as possible in 15 seconds without using hand support. Performance for each leg stepping is assessed separately, and the lowest score will be recorded. The Timed Up and Go (TUG) test will be used to assess mobility [36]. Participants will be seated in a chair with arms resting on the arm rests and asked to get up and walk three meters as fast and safely as they can, turn around and return to a seated position. Functional lower limb strength will be measured using the sit-to-stand test (five chair stands) [37], with participants instructed to stand up and sit down as quickly as possible with or without use of their arms. Maximum voluntary hand grip strength (both hands) will be assessed using a Smedleys dynamometer [34]. The participant will stand against a wall. Holding the dynamometer vertically above the head, the participant will be instructed to squeeze as hard as possible while bringing the arm back down to their side. A 2-minute walk around a 20-metre measured course will be utilized to assess cardiovascular endurance [38]. Participants will be instructed to walk as fast as possible around the course as many times as they can in two minutes. Participants will be allowed to stop walking during the testing period if they needed to, and any rests will be included in the total 2-minute test period. The maximum distance walked, heart rate and rate of perceived exertion [39] will be recorded.

Physical activity will be assessed using the Community Healthy Activities Model Program for Seniors (CHAMPS) physical activity questionnaire [40]. Assessment will be made of the frequency, minutes, and calorie expenditure per week of all, low, moderate, high and very high intensity activities.

Participants will be provided with a pedometer (Digi-Walker SW-200, Yamax Inc., Tokyo, Japan) and asked to wear it for five weekdays and the weekend, following the baseline visit, to objectively measure their weekly PA. The pedometer will be put on immediately upon wakening and taken off just before retiring at night. It will also be removed whilst bathing or showering and the time off recorded on the pedometer diary. Participants and carers will be shown how to wear and use the pedometer and how to complete the diary. Participants will be instructed to maintain their usual activity pattern during the monitoring period.

The stage of PA behavior will be assessed using the Stage of Change Instrument (SCI), a five-item questionnaire asking participants to indicate their current level of activity [41]. The frequency and minutes per week of regular moderate intensity PA will also be measured using this questionnaire.

Exercise self-efficacy will be assessed with the five-item Self-Efficacy Questionnaire (SEQ) asking participants how confident they were to exercise in certain adverse conditions with responses on a 5-point scale ranging from "not at all sure" to "very sure" [42].

Satisfaction with Life will be measured using a five-item questionnaire with responses on a seven-point scale ranging from "strongly disagree" to "strongly agree" [43].

### DNA Sample Collection

APOE genotyping will be performed at baseline testing to adjust for APOE genotype in the final analysis and to investigate whether there is an interaction between APOE genotype and the benefits of PA influencing the primary and secondary outcomes. Participants will be asked to provide a 2 ml saliva sample using a DNA self-collection kit (Oragene DNA OG-250 Disc Format, DNA Genotek Inc, Ontario, Canada). They will be stored at -80°C at the Department of Clinical Pathology and Biochemistry at the Royal Perth Hospital. Samples from Brisbane and Melbourne will be mailed to Perth. All samples will be batched and processed once the final baseline assessment has been completed.

### Randomization and Blinding

Random allocation to intervention or control group will be performed using Stata and the user-written program ralloc [44]. Allocation numbers will be drawn by an investigator not directly involved in the recruitment or assessment of participants. Each of the three study sites will be provided with sealed opaque envelopes numbered 1-100 and used in that order. After a participant completes his/her baseline assessment, the PA RA will open the next consecutive envelope. Inside the envelope there will either be the letter A (physical activity group) or B (control group). Due to logistic difficulties, participants will not be blind to the intervention and sham PA will not be used. However, the "clinical staff" involved in the collection of endpoints will not be aware of group allocation (single blind). Blinding will be supported by the performance of cognitive and physical assessments at different locations and explicit instructions to participants and clinical research staff not to discuss issues related to PA during the assessments. The PA RA will inform participants of their group allocation by telephone and will instruct them not to share that information with research staff involved in their future cognitive assessments.

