### Intervention

The intervention period will be 24 weeks. The intervention will comprise three components: the PA program, the behavioral intervention package, and telephone monitoring. Participants randomized to the intervention will return with their carer ("coach") for a PA workshop within two to four weeks of their baseline visit. During this 60-minute session, the PA RA will give participants their program manual and explain the participants' PA program and the behavioral intervention package.

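### The claim that staff collecting endpoints are blind to allocation is untrue for physical function, which the PA research assistant tests after opening the envelope and delivering the program

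*Protocol article*

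**What the plan says.** Under Randomization and Blinding, the article accepts that participants cannot be blinded, but says that the clinical staff (a term it sets in quotation marks and does not define) "involved in the collection of endpoints will not be aware of group allocation (single blind". The same section gives the PA RA two tasks that reveal the arm: after baseline, "the PA RA will open the next consecutive envelope", and then "The PA RA will inform participants of their group allocation by telephone". Under Intervention, at the workshop, "the PA RA will give participants their program manual and explain the participants' PA program and the behavioral intervention package". The Behavioral Intervention section also has the PA RA mail the motivational newsletters.

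The Assessments section says that, to protect the blinding of the Cognitive RA, "the physical assessments will be conducted by a separate PA RA". The section on the PA RA's measures covers the step test, Timed Up and Go, sit-to-stand, grip strength and two-minute walk, followed by the activity and self-efficacy questionnaires. Table 1 schedules these at baseline, 24 weeks and 52 weeks.

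The abstract includes among the secondary outcomes "carer burden and physical function (strength, balance, endurance, physical activity").

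**The concern.** A reader of the blinding sentence would take every endpoint to be measured by someone who does not know the arm. For physical function, the assessor is the person who has opened the envelope and presented the program. The performance tests ask for maximal speed, distance or force, so the result can move with the assessor's tone and encouragement. In sit-to-stand the participant is "instructed to stand up and sit down as quickly as possible with or without use of their arms", and the article states no rule that keeps the method the same between visits. At stake is how far a difference in strength, balance or endurance can be credited to the program. The analysis described under Statistical Methods (imputation and mixed models) cannot separate an assessor effect that differs between arms from a treatment effect.

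**Working it through.** The article gives no figure on this point, so the check sets its statements side by side.

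| Question | What the article says | Section |
|---|---|---|
| Who is said to be blind? | Staff collecting endpoints, without limit to type | Randomization and Blinding |
| Who opens the envelope and announces the arm? | PA RA | Randomization and Blinding |
| Who runs the workshop? | PA RA | Intervention |
| Who mails the motivational newsletters? | PA RA | Behavioral Intervention |
| Who does the physical tests? | PA RA, separate from the Cognitive RA | Assessments; Measures administered by the PA RA |
| When? | Baseline, 24 and 52 weeks | Table 1 |
| Is physical function an outcome? | Yes, secondary | Abstract |
| From whom must participants hide their arm? | Staff doing the cognitive assessments | Randomization and Blinding |

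**Step 1: timing.** The envelope is opened after the baseline assessment is complete. Baseline tests are therefore done before the PA RA knows the arm, and both follow-up tests are done afterwards. Any assessor effect that differs by arm would enter at follow-up only and so pass into the change from baseline.

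**Step 2: extent.** There are five performance tests (step test, Timed Up and Go, sit-to-stand, grip, two-minute walk) at two follow-up visits: 5 × 2 = 10 scheduled test occasions per participant with an assessor who knows the arm. No other assessor is named for them. Physical activity, the remaining part of the abstract's definition, is measured by the CHAMPS questionnaire, also given by the PA RA. There the participant's own knowledge of the arm would remain whoever administered it.

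**Step 3: what is not affected.** The ADAS-cog and the nine measures described with it belong to the Cognitive RA. That person is kept blind by separate staff, different locations and instructions to participants. One of the nine, the reading test, is taken at baseline only, which leaves 9 − 1 = 8 after baseline. By the article's descriptions, seven of these (all but the SMMSE) draw wholly or partly on carer or participant ratings. That concerns the respondent; the assessor is still blind.

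**Step 4: a conflict over the outcome list.** The section on the Cognitive RA's measures says that its nine assessments make up the secondary outcomes, and no physical test is among them. The abstract says otherwise. The two need to agree, because they decide whether the unblinded tests count as secondary outcomes. This point rests on the abstract, which is explicit.

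**The case against.** The strongest reply is that the intended scope can be read from the article. The assessments are split in order to keep the Cognitive RA blind, the concealment instruction names cognitive assessors only, and the PA RA's knowledge of the arm is disclosed in the same paragraph as the blinding statement. This stands as an account of what was probably meant, and nothing here suggests concealment. It does not rescue the sentence, which speaks of endpoints in general while the abstract lists a whole outcome domain outside the protected set.

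A second reply is that all PA RAs are trained by one chief investigator to standardise procedures. That helps agreement between sites, but it does not stop one assessor from treating the two arms differently.

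Some stronger readings are tempting:

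- A reader might infer that only the ADAS-cog and SMMSE are assessor-blind, because most other cognitive-visit measures rely on carers or participants. The article does not support this: the Cognitive RA is blind for all of them. Awareness among respondents is inherent in an exercise trial without a sham, and it is already disclosed for participants.
- A reader might infer that the physical results will be presented as blinded, or that bias towards benefit is certain. No text says the first. The second is a plausible direction, but not one the document demonstrates.

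**Conclusion.** The blinding statement is untrue as written for the physical-function outcomes and should be corrected. The defect covers the five performance tests at 24 and 52 weeks. The CHAMPS activity measure shares the unblinded assessor but is self-reported in any case. The size of any bias cannot be worked out from the article.

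The primary outcome is not touched, and the carer and participant ratings taken by the Cognitive RA keep a blind assessor. The point is therefore moderate: it limits what can be concluded for one secondary domain and does not threaten the main result.

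The conclusion rests on two readings: that the abstract's list of secondary outcomes holds, and that the PA RA who allocates and delivers at a site is also the one who tests there, since the article names no other.

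**What to change.** - Restate the blinding as applying to the measures administered by the Cognitive RA, and note that some of these depend on respondents who know the arm.
- State that outcomes administered by the PA RA are assessed unblinded, and interpret them as supportive.
- Reconcile the abstract with the section that lists nine secondary measures, so that the status of physical function is clear.
- Give the PA RA a fixed test script without encouragement. Record arm use in sit-to-stand at baseline and keep it the same at follow-up.

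The tests should not be moved to the Cognitive RA. That would undo the separation of staff and locations and could unblind the rater before the 52-week ADAS-cog.

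The cost is protocol wording, a short script, one recorded item and a more cautious claim on physical function. Sample size and visit schedule do not change.
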